
Numerous other approaches are commonly utilised in clinical settings, but a formal demonstration of their efficacy remains to be shown. Clinical approaches for cervical radiculopathies commonly include interventions targeting the opening of intervertebral foramen [26]. It is well recognised that cervical movements causing the opening of intervertebral foramen, such as flexion, rotation and lateral flexion contralateral to the nerve root, increase the volume of the foramen, and consequently might decompress a swollen nerve root [27-31]. Inversely, movements of extension, rotation and lateral flexion ipsilateral to the nerve root close the intervertebral foramen around the root. Thus, for acute and sub-acute radiculopathies, intervention programs should include treatment modalities that allow the opening of the intervertebral foramen. On the other hand, movements and positions that lead to intervertebral foramen closure should be avoided. However, no studies have evaluated the effects of a treatment approach that specifically take into consideration these biomechanical principles. Due to the important incapacities related to cervical radiculopathy, and to the few studies pertaining to the efficacy of rehabilitation in this population, we believe in the importance of better understanding the potential of cervical mobilisations and exercises that lead to the opening of the intervertebral foramen. The primary objective of this RCT is to compare, in terms of pain and disability, a rehabilitation program targeting the opening of intervertebral foramen to a conventional rehabilitation program, in patients presenting acute or subacute cervical radiculopathies. Based on biomechanical principles, our hypothesis is that the rehabilitation program targeting the opening of intervertebral foramen will be significantly more effective in reducing pain and disability than the conventional rehabilitation program, mainly at the 4-week evaluation. In considering the passage of time, the differences between the two interventions should be less important at 8-week.

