### Outcome measures (dependent variables)

The NDI questionnaire has been chosen as the primary outcome measure. All evaluations will be undertaken at the CIRRIS. Here is a description of the outcome measures:

*Neck Disability Index: *The NDI is a 10-item questionnaire that measures a patient's self-reported neck pain related disability. Questions include activities of daily living, such as: personal care, lifting, reading, work, driving, sleeping, recreational activities, pain intensity, concentration and headache. The questions are measured on a six-point scale from 0 (no disability) to 5 (full disability). The numeric response for each item is summed for a total score ranging from 0 to 50 [32]. A higher NDI score indicates a greater patient's perceived disability. The reliability (intraclass correlation coefficient [ICC]: 0.73 to 0.98), construct validity, and responsiveness to change have all been demonstrated in various populations [32]. For patients with cervical radiculopathy, the minimal detectable change is 10 points, and the clinically important difference is 7 points [33]. The validated French version of the NDI will be used [34].

*Disabilities of the Arm, Shoulder and Hand: *The *Quick*DASH is a region-specific questionnaire that evaluates the physical disability and symptoms of the upper limb in patients with upper extremity disorders [35]. It consists of 11 items extracted from the original 30-item DASH. Each item has five response choices, ranging from "no difficulty or no symptoms" to "unable to perform activity or very severe symptoms," and is scored on a one-to-five scale. To calculate a *Quick*DASH score at least 10 of the 11 items must be completed. The score ranges from 0 (no disability) to 100 (most severe disability). The validity, reliability (ICC = 0.96) and responsiveness of the *Quick*DASH have been established [36]. The minimal detectable change is 10.8% and the clinically important difference is 10.2% [36]. The *Quick*DASH is also valid for the measurement of upper extremity disability in patients presenting neck pain [37]. The validated French-Canadian version of the *Quick*DASH will be used [38].

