### Sample size and Analyses

The sample size calculation is based on the primary outcome measure, the NDI. The NDI has a clinically important difference of 7/50 (14/100) points for patients presenting a cervical radiculopathy. The standard deviation reported in the literature for this population is 18.4 [33]. The considered parameters are 0,05 for type I error (α) with a power of 0,80 (1-β). For an analysis of variance (ANOVA), the sample size required is 16 subjects per group. However, 18 subjects per group will be recruited to compensate for withdrawals and probable loss of follow-up. This sample size will provide sufficient power to detect a clinically important difference between the two groups.

Descriptive statistics (mean, standard deviation, median frequency counts) will be calculated for all outcome measures at the different times of measurement (week 0, 4 and 8) to summarise results. Baseline demographic data will be compared (independent Student t-tests and Chi-squared tests) across groups to establish the comparability of covariables. If needed, statistical adjustments will be made for baseline characteristics that are significantly different between groups. All data will be tested to ensure they meet the assumptions for the inferential statistical analyses. If they do not meet the necessary assumptions, appropriate non-parametric procedures will be used. An intention-to-treat analysis will be used in which all participants will be analysed in the group to which they were originally assigned. All dropouts and the reason for dropping out of the study will be reported. Any harms or unintended effects during the rehabilitation programs will be recorded, reported and discussed.

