A mixed-model, 2-way ANOVA (Groups [experimental program, conventional intervention] × Evaluation [week 0, 4 and 8]) will be used to analyse the effects of the rehabilitation programs. Separate analyses will be conducted on each of the primary (NDI) and secondary (*Quick*DASH, NPRS, cervicothoracic range of motion) outcomes. If an interaction is detected (*P *< 0.05), simple effects will be examined. The Kolmogorov-Smirnov test (*P *< 0.05) will be conducted on the different scores to ensure normality for all variables with significant main effects. For normally distributed variables with significant main effects, post hoc dependent Student *t *tests will be conducted and effect sizes (Cohen's *d*) will be calculated. Effect sizes will be interpreted as small (0.20), medium (0.50), or large (0.80). For any variables that will not be normally distributed, the Wilcoxon signed-rank test and Glass's delta (effect size) will be used for post hoc contrasts. Since this study is looking at a new rehabilitation program, patient's perceived change following the programs will also be categorised as either success or failure. Success will be defined as a 50% improvement in NDI score and a GRC score rated as "moderately better" (+3) or higher. Patients will be classified as failure if the change on the GRC is "somewhat better" (+2) or at any level below this or if there is not a 50% improvement in the NDI [49]. The proportion of success/failure will be compared across groups (Chi-squared tests).

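### The primary NDI test is a gated 2-df interaction with baseline as an outcome level: valid, but less powerful than a baseline-adjusted comparison at week 4, where the hypothesis mainly lies

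*Protocol article*

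**What the plan says.** - **Primary outcome** (Outcome measures): "The NDI questionnaire has been chosen as the primary outcome measure".
- **Hypothesis** (Background, last paragraph): the experimental program will reduce pain and disability more "than the conventional rehabilitation program, mainly at the 4-week evaluation", and "the differences between the two interventions should be less important at 8-week".
- **Analysis** (Sample size and Analyses): a mixed-model two-way ANOVA of group by "Evaluation [week 0, 4 and 8]) will be used to analyse the effects of the rehabilitation programs", run separately for the NDI and for each continuous secondary outcome.
- **Gate** (same section): simple effects are examined "If an interaction is detected" at P < 0.05. The post hoc tests named after significant main effects are paired, within-patient tests, so they do not compare the programs.
- **Baseline** (same section): adjustment is planned only for baseline characteristics that turn out significantly different between groups. Baseline NDI is not a prespecified covariate.
- **Sizing** (same section): "The NDI has a clinically important difference of 7/50 (14/100) points for patients presenting a cervical radiculopathy". The calculation pairs this with a published SD of 18.4. Alpha is 0.05 and power 0.80. The result is 16 per group, with 18 recruited.

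**The concern.** The hypothesis is about a between-group difference concentrated at one visit, and the sample size rests on a single between-group difference. The test is a 2-df omnibus over three visits. One of those visits precedes assignment, so its expected group difference is zero. The omnibus spreads its sensitivity over every time pattern, including patterns nobody expects. The week-4 comparison is reached only when the omnibus is significant. The interaction P value also gives no estimate or confidence interval for the week-4 difference.

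With 36 patients, a real week-4 benefit of the planned size could be missed more often than necessary, purely through the choice of test.

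**Working it through.** **Inputs from the protocol.** Difference 14/100; SD 18.4; alpha 0.05; 16 needed and 18 recruited per group; visits at weeks 0, 4 and 8.

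**Assumptions, because the protocol does not give them.** The SD is on the 0–100 scale, tests are two-sided, variances are equal at all visits, and correlation is compound symmetric. The between-visit correlation r runs from 0.3 to 0.8. The week-8 difference is 7 in the main case, with 10.5, 14 and 0 as alternatives.

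**1. The plan's own figure.** d = 14/18.4 = 0.761. For two unadjusted means, n = 2(1.960 + 0.842)²/0.761² ≈ 27.1, so 28 per group (29 by the exact non-central t). The stated 16 is not reproduced. An unadjusted two-group t-test has power 0.55 at 16 per group and 0.60 at 18. This is a separate issue; it matters here because it shows there is little power to spare.

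**2. Planned interaction test.** Degrees of freedom are (2−1)(3−1) = 2 and 4n − 4 = 68. The non-centrality is λ = (n/2) Σ(δ_t − mean δ)² / [SD²(1 − r)], where δ_t is the group difference at visit t. For 0/14/7 the mean is 7 and the sum of squares is 49 + 49 + 0 = 98. At r = 0.5, λ = 9 × 98 / (338.56 × 0.5) = 5.21, and power is 0.50.

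**3. Baseline-adjusted week-4 contrast.** The residual SD is SD√(1 − r²), with 2n − 3 = 33 df. The variance of the difference is SD²(1 − r²)(2/n), multiplied by 1 + 1/(2n − 4) for chance baseline imbalance. At r = 0.5 the variance is 338.56 × 0.75 × (2/18) × (1 + 1/32) = 29.09, the standard error is 5.39, and non-centrality is 14/5.39 = 2.60. Power is 0.71.

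**4. Results at 18 per arm, differences 0/14/7**

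| r | Interaction | Adjusted week 4 | Loss (points) |
|---|---|---|---|
| 0.3 | 0.375 | 0.628 | 25 |
| 0.5 | 0.502 | 0.712 | 21 |
| 0.6 | 0.601 | 0.779 | 18 |
| 0.7 | 0.735 | 0.863 | 13 |
| 0.8 | 0.895 | 0.953 | 6 |

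Simulation with 20,000 runs per setting agrees to within about 0.01.

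**5. Sensitivity to the week-8 difference** (interaction power, loss in points in brackets)

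| r | Week 8 = 10.5 | Week 8 = 14 or 0 |
|---|---|---|
| 0.3 | 0.402 (23) | 0.482 (15) |
| 0.5 | 0.537 (17) | 0.631 (8) |
| 0.7 | 0.771 (9) | 0.855 (1) |
| 0.8 | 0.918 (4) | 0.963 (−1) |

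Full persistence and complete disappearance give the same λ, because Σ(δ_t − mean δ)² is 130.67 in both.

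**6. Effect of the gate.** The protocol does not name the simple-effect test. If it is an unadjusted week-4 t-test, its power alone is 0.60. Requiring the interaction to be significant as well gives 0.38 at r = 0.5 and 0.49 at r = 0.7 (simulated, 0/14/7).

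**7. Validity.** With no true difference, the interaction rejects in about 5% of simulations under compound symmetry, and in 5.5% under an unequal correlation pattern.

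**The case against.** **The interaction is a recognised treatment test in a randomised pre–post design.** This stands. Its type I error is right, so a reader who infers that the analysis is invalid goes too far.

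**Baseline is not ignored.** This stands too. The interaction uses baseline through within-patient contrasts. Under 0/14/7 it equals an unadjusted week-4 t-test (0.60) at r = 0.6 and beats it above that. At r = 0.5, about 11 of the 21 points lost (0.71 against 0.60) come from the missing covariate and about 10 (0.60 against 0.50) from the omnibus form.

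**The size of the loss rests on unstated inputs.** It would be tempting to say that the plan discards much of its power whatever the truth. The protocol gives neither the correlation nor the week-8 effect, and at r = 0.8 with full persistence the order even reverses slightly. But the hypothesised pattern is smaller at week 8, neither equal nor absent, and there the loss is 4 to 25 points across the range examined.

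**The group main effect averages in a null baseline difference.** A reader might conclude that the trial will be judged on that weak test. The protocol does not name it as the treatment test; group comparisons run through the interaction and simple effects.

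**The hypothesis says mainly, not only, week 4, and gating limits follow-up tests.** Fair: a three-visit analysis is defensible, and the gate bites only when the interaction is non-significant. Naming one primary contrast controls multiplicity just as well.

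**Details may sit in an unshown analysis plan.** Covariate lists often do. But the article itself states the test and the gate, and those are what conflict with its hypothesis.

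**Conclusion.** The point holds as one of efficiency and alignment, not validity. The stated test does not target the week-4 difference that the Background puts first, and reaching that comparison depends on an omnibus result. Under the hypothesised pattern, taken as 14 points at week 4 and 7 at week 8, the interaction loses about 25 points of power at r = 0.3, falling to about 6 at r = 0.8, against a baseline-adjusted week-4 contrast in the same patients. The loss is smaller if more of the effect persists, and about zero at r of 0.7 or more if it fully persists or vanishes. These figures assume SD 18.4 on the 0–100 scale, two-sided 5%, compound symmetry and 18 analysed per arm.

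A reader might infer that changing the analysis rescues the stated 80% power. It does so at 18 per arm only if r exceeds about 0.6. The sample-size figure needs its own correction.

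**What to change.** - Define the primary analysis as the between-group difference in NDI at week 4, adjusted for baseline NDI: 1 df, two-sided 5%, reported with a 95% CI.
- Estimate it by ANCOVA at week 4, or from a mixed model on the week-4 and week-8 scores with group, visit, group × visit, baseline NDI and baseline × visit.
- Do not make it conditional on the interaction. Name week 8 as the secondary contrast.
- Use the same form for QuickDASH, NPRS and range of motion.
- Prespecify the baseline NDI covariate, so that adjustment for it does not depend on a baseline significance test.

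The cost is a change of wording, made before any unblinded look at the data; every measurement needed is already scheduled. The small downside is that the week-8 difference no longer contributes to the primary test.

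### A Kolmogorov-Smirnov switch with little power at 18 per group picks the post hoc paired test, and a separate open fallback leaves the primary NDI test dependent on assumption checks

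*Protocol article*

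**What the plan says.** All of the relevant text is in the protocol article, section Sample size and Analyses.

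- Main analysis: "A mixed-model, 2-way ANOVA (Groups [experimental program, conventional intervention] × Evaluation [week 0, 4 and 8]) will be used", run separately on NDI and on each secondary outcome. If the interaction is significant, simple effects follow.
- Normality check: after that model, a K-S test at the 0.05 level "will be conducted on the different scores to ensure normality for all variables with significant main effects".
- If normality is accepted: "For normally distributed variables with significant main effects, post hoc dependent Student" t tests, with Cohen's d.
- If it is rejected: "For any variables that will not be normally distributed, the Wilcoxon signed-rank test and Glass's delta (effect size) will be used for post hoc contrasts".
- Earlier in the section there is a general promise, "All data will be tested to ensure they meet the assumptions for the inferential statistical analyses", followed by a general fallback: "If they do not meet the necessary assumptions, appropriate non-parametric procedures will be used". Neither sentence names a test, the quantity to be tested or the replacement procedure.
- Size: "the sample size required is 16 subjects per group", and "18 subjects per group will be recruited to compensate for withdrawals and probable loss of follow-up". The check therefore sees 18 values per group, or 36 if the groups are pooled, before any withdrawals.

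**The concern.** Three features of the K-S step are unsound.

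1. **Purpose.** It is meant to ensure normality, but a non-significant goodness-of-fit test at 18 per group is weak evidence of anything. If the test rarely rejects whatever the shape, it adds little except the appearance of a check.
2. **Target.** A paired t test relies on the distribution of within-patient differences. The text speaks of scores and of normally distributed variables, and mentions neither differences nor residuals.
3. **Data dependence.** The reported P value and the effect-size measure both change with the outcome of the check. Two outcomes in one table could carry Cohen's d and Glass's delta side by side. Glass's delta is still a mean difference divided by a standard deviation, so moving to it does not deal with non-normality. It only makes the figures harder to compare.

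The general fallback has wider reach. It covers all inferential analyses, so it also covers the NDI comparison. What is at stake there is whether the test of the primary outcome is settled before the data are seen.

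**Working it through.** The plan gives no figure for the performance of its normality check, so there is none to reproduce. The check was simulated at the plan's own sample sizes.

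**Inputs from the protocol:** n = 18 per group and 36 in total; K-S at P < 0.05.

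**Assumptions:** the article gives no distribution for NDI or the other scores, so the shapes are illustrative: normal, chi-square with 4 df (skewness 1.4) and exponential (skewness 2). The article does not say which K-S version is meant, so two were run.

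**Step 1. Rejection rate of the check.** For each sample, D = max |F_n(z) − Φ(z)| with z = (x − mean)/SD, mean and SD being estimated from that sample. The classical version refers D to the standard K-S distribution. The corrected (Lilliefors-type) version uses the simulated 95th percentile of D under normality. Each case had 2,000 to 5,000 runs. Ranges cover repeated simulations.

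| n | Shape | Classical K-S | Corrected K-S | Shapiro-Wilk |
|---|---|---|---|---|
| 18 | normal | 0% | 5–6% | about 5% |
| 18 | chi-square(4) | 0.6–1.0% | about 30% | 46–47% |
| 18 | exponential | 2.5–4% | 51–53% | 76–78% |
| 36 | normal | 0% | 5–6% | about 5% |
| 36 | chi-square(4) | 3–4% | 53–54% | 83–85% |
| 36 | exponential | 18–19% | 84–86% | 99% |

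The classical version rejects 0% of normal samples instead of 5%, because estimating the mean and SD makes it very conservative. At 18 per group the corrected version still misses 100 − 30 = 70% of the chi-square(4) samples and about 100 − 51 = 49% of the exponential ones.

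**Step 2. Does it matter which quantity is tested?** n = 18, corrected K-S, 3,000 runs.

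- Skewed scores, normal change (shared exponential patient effect plus normal visit error): a check on the scores rejects in 47% of samples, a check on the differences in 5%. A score check would often switch to Wilcoxon when the paired t test was in order.
- Normal baseline scores, exponential change: a check on the scores at either visit rejects in 10%, close to the 1 − 0.95² = 9.75% expected from two independent 5% tests. A check on the differences rejects in 54%. A score check would mostly miss the departure that matters.

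**Step 3. Which P values pass through the check?** The K-S step follows the ANOVA and selects only between two paired, within-patient procedures. Neither compares the groups. The group by time F test is computed before the K-S test and does not depend on it.

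**Step 4. What would a missed departure cost?** Null simulations at 18 per group gave these rejection rates at a nominal 5%:

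- Group by time F test: 4.95% (normal), 4.8% (chi-square(4)), 4.9% (exponential).
- Paired t test, 18 patients: 7–8% when the differences are strongly skewed; 4.4% when both visits are exponential but the differences are symmetric.

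**Step 5. The general fallback.** This sentence is not limited to post hoc contrasts or to variables with significant main effects. Read as written, it allows the NDI ANOVA itself to be replaced if unspecified assumption tests fail.

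**The case against.** The strongest counter-argument is that little of importance hangs on the K-S step. A reader might infer from it that the primary between-group NDI test is chosen by a near-powerless pre-test. The text does not support that: the ANOVA is named, applied to NDI and run first, and the K-S result governs only paired contrasts and effect sizes. The F test also holds its level under the skewed shapes tried. All of this stands.

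A reader might also infer that the ANOVA's assumptions are never examined. The general promise to test all data contradicts that, although it sits awkwardly beside a K-S test limited to variables already found significant.

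Third, the phrase about the different scores need not mean raw scores. Beside paired tests it could be a slip for difference scores, which would be the right quantity. The later reference to normally distributed variables favours the plainer reading, but the wording is ambiguous and raw scores should not be asserted as fact.

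Fourth, describing the check as powerless is too strong in general: a corrected K-S test on all 36 patients finds exponential skew about 84 to 86% of the time.

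Finally, an article may leave the name of a fallback procedure to a fuller document. That is fair, and the missing name is not the complaint. The complaint is that the article itself fixes a rule under which the choice of test depends on assumption tests.

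**Conclusion.** The point holds in limited form. The K-S switch cannot do what the protocol says it is for at 18 per group, and as worded it does not target within-patient differences. It makes the post hoc test and effect-size measure data-dependent. Its reach ends at the post hoc paired contrasts. The primary NDI comparison is left data-dependent by the general non-parametric fallback, not by the K-S step.

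Severity is minor to moderate. The simulations show no inflation of the group by time test. The paired contrasts could run at 7 to 8% instead of 5% under strong skew in the differences. These sizes rest on assumed distributions, no withdrawals and an unstated K-S version; the range between the classical and corrected versions is wide, but neither gives assurance of normality at 18 per group.

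**What to change.** In Sample size and Analyses:

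1. Delete the K-S step, and remove the general non-parametric fallback for NDI.
2. Name one between-group NDI model, adjusted for the baseline NDI that is already collected, and keep it whatever the distribution. Inspect residual plots and report them, without letting them change the test.
3. Name one robust sensitivity analysis of the group effect and run it in every case: a permutation test of the adjusted effect, or rank ANCOVA.
4. For the post hoc paired contrasts, state one method and one effect-size measure for all outcomes.

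No data collection, visit or sample size changes. The cost is a few sentences and one extra sensitivity analysis. The gain is that no reported test is selected by looking at the data.

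### Effect sizes depend on significance and are tied to within-subject tests, so the plan fixes no unconditional between-program NDI estimate with its precision

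*Protocol article*

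**What the plan says.** All of this is in the Protocol article, Sample size and Analyses. The model is a Group (2) × Evaluation (weeks 0, 4, 8) ANOVA, run separately for the NDI and each secondary outcome.

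- Simple effects have a condition: "If an interaction is detected" at P < 0.05.
- Effect sizes have a different condition. For normally distributed variables "with significant main effects, post hoc dependent Student *t *tests will be conducted and effect sizes (Cohen's *d*) will be calculated". Otherwise, "the Wilcoxon signed-rank test and Glass's delta (effect size) will be used for post hoc contrasts".
- Two items have no significance condition. One is the set of summaries: "Descriptive statistics (mean, standard deviation, median frequency counts) will be calculated for all outcome measures at the different times of measurement". The other is the responder analysis: "The proportion of success/failure will be compared across groups", for which only a chi-squared test is named.
- The sample size rests on a between-group quantity: "The NDI has a clinically important difference of 7/50 (14/100) points for patients presenting a cervical radiculopathy". The section concludes: "This sample size will provide sufficient power to detect a clinically important difference between the two groups".

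**The concern.** The primary objective is to compare two programs. The result that answers it is the difference between programs on the NDI, with an interval that can be set against 0 and against 7/50. The text instead states a rule for effect sizes that has two faults.

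First, the effect size goes with a paired test. A large within-patient d in both arms is what one expects in acute or subacute radiculopathy, and it says nothing about which program is better.

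Second, whether an effect is quantified depends on a P value. The between-program contrasts are the simple effects, and these are examined only after a significant interaction. If the interaction is not significant, the plan does not lead to a stated difference with its uncertainty, and the result is easily misread as equivalence. If it is significant, the contrast has been selected for being large.

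**Working it through.** **The plan's own figure.** This point rests on no figure in the plan. The nearest is the sample size, whose inputs are used below. The inputs are a difference of 14/100, an SD of 18.4 ("The standard deviation reported in the literature for this population is 18.4"; scale not stated, taken as 0–100 to match 14/100), α = 0.05 (taken as two-sided) and power 0.80. Then n = 2 × (1.96 + 0.8416)² × 18.4² / 14² = 2 × 7.849 × 338.56 / 196 = 27.1, so 28 per group, not 16. That is a separate matter. What counts here is the power of a single-visit two-group t test on these inputs: 0.55 at 16 per group and 0.60 at 18. A non-significant result is quite possible even if the true difference equals the clinically important one.

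**Step 1: what each route yields.**

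| Route in the text | Condition | What it quantifies |
|---|---|---|
| Cohen's d with dependent t test | significant main effect | change within patients |
| Glass's delta with signed-rank test | non-normal variable, post hoc | change within patients |
| Simple effects | significant interaction | may include program differences; no interval stated |
| Visit means and SDs | none | crude difference by subtraction |
| Success proportions | none | chi-squared test; no risk difference or interval stated |

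No row gives an unconditional between-program NDI estimate with its precision.

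**Step 2: what can be recovered from visit means and SDs.** For one visit, the 95% half-width is t × SD × √(2/n).

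- n = 18: 2.032 × 18.4 × √(2/18) = 12.5/100 = 6.2/50.
- n = 16: 2.042 × 18.4 × √(2/16) = 13.3/100 = 6.6/50.

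So at 18 per group a non-significant advantage above 7 − 6.2 = 0.8 points on the 50-point scale still has an interval reaching 7/50. Baseline adjustment multiplies the half-width by about √(1 − ρ²), where ρ is the correlation with baseline. From 12.5 this gives 11.9, 10.8 and 8.9 for ρ = 0.3, 0.5 and 0.7. Visit means and SDs do not reveal ρ, so a reader cannot recover the adjusted interval from them.

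**Step 3: does the condition distort the program difference?** The 2 × 3 ANOVA was simulated 6,000 times per setting with 16 per group, SD 18.4 and equal correlation between visits. Control improvement was assumed to be 10 and 14 points at weeks 4 and 8, and the program effect was the same at both visits. The quantity is the mean between-program difference in change to week 4, on the 0–100 scale.

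| ρ | Interaction power (true 14) | Mean after significant interaction | Ratio to 14 | Mean after significant Evaluation effect |
|---|---|---|---|---|
| 0.3 | 0.43 | 19.4 | 1.38 | 13.9 |
| 0.5 | 0.57 | 17.5 | 1.25 | 13.95 |
| 0.7 | 0.81 | 15.4 | 1.10 | 14.0 |

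The Evaluation effect is significant in practically all trials with a true 14 and in 92–100% with no program difference, so conditioning on it changes nothing. With no control improvement (ρ = 0.5), some main effect is significant in 75% of trials and the conditional mean is still 14.05. For a true 7/100, the interaction-conditioned means are 16.2, 13.9 and 11.9, or 2.3-, 2.0- and 1.7-fold.

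**Step 4: the same for an unadjusted week-4 contrast.** The group average over the three visits is independent of the interaction test, and its expected difference is 2 × 14/3 = 9.33. By symmetry of weeks 4 and 8, the interaction contributes one third of the conditional difference in change. The conditional week-4 difference is then 9.33 + 19.38/3 = 15.8 (1.13-fold) at ρ = 0.3 and 9.33 + 15.44/3 = 14.5 (1.03-fold) at ρ = 0.7. The 1.1- to 1.4-fold range therefore belongs to differences in change. A raw week-4 comparison is distorted less.

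**The case against.** Four points can be made for the plan.

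1. **A reader might infer that a non-significant NDI result leaves no estimate at all.** The article does not support that. Means and SDs are planned for every outcome at every visit without condition, and step 2 shows that a crude difference and interval follow from them. The success proportions are also compared whatever the other tests show. What stays missing is a planned, baseline-adjusted difference with its interval.

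2. **A reader might infer that the reported effect sizes are inflated in general.** They are not shown to be. The stated condition is a significant main effect, Evaluation is one of the main effects, and step 3 finds no inflation of the program difference under it. Exaggeration arises only where the between-program contrast is reached through the interaction. This does not rescue the rule, because on the lenient reading the d is a within-patient measure.

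3. **A reader might picture an effect-size table holding only favourable outcomes.** No such table is planned, and a significant main effect may favour either program or only reflect improvement in both.

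4. **An article may leave intervals and reporting format to an analysis plan that is not shown.** This is fair for format and for the absence of a risk difference taken alone. It does not cover a rule the article itself states: effect sizes follow significance and accompany paired tests.

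**Conclusion.** The point holds in this limited form. The stated rule quantifies effects only after significance and, where it does so, measures change within patients. The plan therefore fixes no unconditional between-program estimate with its precision for the primary NDI, although that is the quantity the trial was sized on. That conclusion needs no assumption beyond the text.

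The size of any distortion does rest on assumptions: SD 18.4 on the 0–100 scale, 16 per group, equal visit correlations of 0.3–0.7, and an equal program effect at weeks 4 and 8. Under these, differences in change examined only after a significant interaction are overstated about 1.1- to 1.4-fold for a true 14/100. They are not overstated when the condition is the Evaluation main effect. It is a point that should be corrected, not one that invalidates the trial.

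**What to change.** Remove significance as the condition for effect estimates. State that for the NDI, and likewise for the QuickDASH, NPRS and range of motion, the baseline-adjusted between-group mean difference at weeks 4 and 8 will be reported with its 95% CI whatever the P value. For success, report the risk difference with its 95% CI beside the chi-squared test. Interpret the NDI interval against both 0 and 7/50. Within-patient effect sizes may stay if they are labelled as change over time.

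The cost is a sentence or two in the analysis section. The data are already collected at all three visits, and no further patients are needed.
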